## **Statistical analysis used in final manuscript.**

### **1. Statistical methods (details of primary analyses)**

Analyses were performed using Stata version 18 (Stata Corporation, Inc., College Station, TX, USA) and a two-sided P value of 0.05 was deemed statistically significant.

Normality was assessed by examining the distribution of residuals, and homogeneity of variance was evaluated through visual inspection of plots of residuals versus fitted values.

#### **1. Linear Mixed Effects Model (Repeated-measures mixed-effects model)**

We chose mixed-effects models for the primary analyses because they are well-suited to handle longitudinal data with repeated measures over time. These models account for the correlation within subjects by including random effects, which allows each participant to serve as their own control and reduces bias arising from individual differences. Moreover, mixed-effects models are flexible in accommodating missing data under the assumption that data are missing at random. Importantly, no imputation procedures for missing data were performed, as these were not pre-specified in the original study protocol.

STATA functions used: -mixed function in STATA (version 18) was used for the modelling of linear mixed effects model. The -margins command was used to calculate the estimated value of the outcome measure at each time point. The -lincom function was used to calculate the within- and between-group differences over time.

The outcomes for which we used linear mixed effects models were visual analog scale (VAS) knee pain, Western Ontario and McMaster University Index (WOMAC) subscales (pain, function, and stiffness), patient global assessment, Depression (as assessed by patient health questionnaires), quality of life derived utility values, core physical performance measures (as assessed by 30 s chair stand test, 40 m fast walk test, and stair climb test), neuropathic pain (as assessed by painDETECT questionnaire) and leg muscle strength. First, the main effects are treatment group, time, and interaction of treatment group with time. The presence of time interaction allows us to estimate the treatment effect at different time points (each follow-up). Second, the model was also adjusted for baseline values for each continuous outcome, age, sex, and BMI. Furthermore, the interaction terms for each confounder with time were added. Third, participant ID was included as a random effect allowing random intercepts. This addresses the correlation within repeated measures. Fourth, the mixed-effects model was fitted using default setting of -mixed function (independent covariance and the restricted maximum likelihood method).

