### **Randomisation and blinding:**

Allocation of participants in a 1:1 ratio to either a 12-week *yoga program* or *strengthening exercise program* will be based on computer-generated random numbers prepared by a statistician with no involvement in the trial. Code-break for the full randomisation schedule will be maintained by the administering institute.

The assessors will be blinded to treatment allocation for objective outcome measures. Allocation concealment and blinding will be ensured by having two research nurses coordinate the trial. Assessments will be taken by the research nurse blinded to the group allocation.

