***Statistical Analyses:***

The comparisons of pain and other continuous scores will be made using a repeated-measures mixed model with terms of treatment, time, and corresponding baseline values as covariates. The effect of treatment will be evaluated by the intervention by time interaction, and then proceed to the main effects model with only group and time. We will also assess the effects of potential confounders or interaction with treatment by covariates, including age, sex, BMI, disease severity, comorbidities, health status, and use of pain medications. A 2-sided P-value less than 0.05 will be considered to indicate the statistical significance, and the results will be shown as the between-group differences with 95% confidence intervals (95% CIs) of the differences.

We will explore the role of clustering effects in the trial by performing a sensitivity analysis examining the implications of clustering by the instructor by adding an instructor random effect to the mixed-effects model.

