**Sample size calculation.**

Our power calculations are based on a sample size that can document the superiority of yoga compared to strengthening exercise by an amount that meets the minimal clinically important difference (MCID). Based on the MCID of 15 mm in VAS pain (a numerical scale ranging from 0 (no problem) to 100 (maximum problem)), the two-sided significance level of 0.05, 90% power, and SD of VAS pain change 22.5, we will need a total of 98 participants.

Assuming a scenario of around 20% dropout, we will need 126 participants. The above sample size will allow us to detect a non-inferiority of yoga with strengthening exercise. Non-inferiority would be declared if the mean change in knee pain (assessed using VAS) in the yoga group was not significantly worse than the mean change in the strengthening exercise group, within a pre-stated margin of non-inferiority (D), in this case, set at 10 mm. Overall, 126 participants will give us 80% power to detect the non-inferiority of yoga compared with strengthening exercise.

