## SAP-summary of changes

Few changes were made, and while not updated in the original protocol, published protocol version and registry.

1. **Original Protocol:** We stated we will explore the role of clustering effects in the trial by performing a sensitivity analysis examining the implications of clustering by the instructor by adding an instructor random effect to our mixed-effects model.

**ANZCTR – Registration:** We will explore the role of clustering effects in the trial by performing a sensitivity analysis examining the implications of clustering by the instructor by adding an instructor random effect to our mixed-effects model.

**Open access protocol publication:** We will explore the role of clustering effects in the trial by performing a sensitivity analysis examining the implications of clustering by the instructor by adding an instructor random effect to our mixed-effects model.

**Final Manuscript:** We did not examine the role of clustering effects in the trial because more than 80% of the yoga classes were conducted by one instructor, and more than 80% of the strengthening exercise classes were conducted by another instructor.

2. **Original Protocol:** We stated we will assess the effects of potential confounders or interaction with treatment by covariates, including age, sex, BMI, disease severity, comorbidities, health status, and use of pain medications.

**ANZCTR – Registration:** We stated we will also assess the effects of potential confounders or interaction with treatment by covariates, including age, sex, BMI, disease severity, comorbidities, health status, and use of pain medications.

**Open access protocol publication:** We stated we will assess the effects of potential confounders or interaction with treatment by covariates, including age, sex, BMI, disease severity, comorbidities, health status, and use of pain medications.

**Final Manuscript:** Regarding the additional adjustments for disease severity that was initially specified in our study protocol, we were unable to include these variables in our final models due to inadequate data. However, we adjusted our model for comorbidities, health status, and use of pain medications, and the results were similar to those of the unadjusted model, so we removed it from the model.

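### The random-intercept primary model can misstate the week-12 standard error in either direction, and the protocol's test-then-average step leaves the primary contrast dependent on the data

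*Combined protocol and SAP*

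**What the plan says.** The analysis used (Statistical analysis used in final manuscript, item 1, Linear Mixed Effects Model) has treatment, time and their interaction, the baseline value, age, sex and BMI, confounder-by-time terms, and a random intercept per participant. On covariance it says that "the mixed-effects model was fitted using default setting of -mixed function (independent covariance and the restricted maximum likelihood method". It names no visit-specific residual variance and no robust SE. The variance check is a visual plot of residuals against fitted values. Estimates come from -margins at each time point, and the -lincom "function was used to calculate the within- and between-group differences over time".

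The original protocol (Statistical Analyses) evaluates treatment by the group-by-time interaction, "and then proceed to the main effects model with only group and time". It gives no significance threshold for the interaction, no rule for a significant result, and no list of the visits that the main effect averages. The SAP text (Data analysis) omits this step. The SAP summary of changes lists three items: clustering, covariates and non-inferiority. The removal of the main-effects step is not among them.

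The primary outcome is change in VAS knee pain over 12 weeks in the outcome lists, but the moderator paragraph of the SAP places it at 12 weeks. VAS is collected at weeks 0, 4, 8, 12, 16, 20 and 24. No document gives SDs or correlations by visit, or says which visits are outcome rows.

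**The concern.** A random intercept with independent residuals gives every visit the same variance and every pair of visits the same correlation. With complete data and treatment-by-visit in the model, the week-12 estimate is close to the ordinary adjusted difference at week 12, but its SE comes from a variance pooled over all modelled visits. If the week-12 variance is above that average the interval is too narrow; if below, too wide. After baseline adjustment, variance tends to rise with time since baseline, because correlation with baseline decays. The answer therefore depends on which visits are in the model.

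The same interval decides superiority and the comparison with the 10 mm margin, so an error in its width affects both conclusions.

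The protocol's two-step rule is a separate problem. An effect at week 12 and an average over visits are different quantities. If a test on the trial's own data chooses between them, the plan has no single primary effect.

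**Working it through.** **The plan's own figure.** The inputs are "Based on the MCID of 15 mm in VAS pain" and "two-sided significance level of 0.05, 90% power, and SD of VAS pain change 22.5, we will need a total of 98 participants"; the protocol also has "Allocation of participants in a 1:1 ratio". The normal formula gives 2 × (1.960 + 1.282)² × 22.5² / 15² = 47.3, so 48 per arm, 96 in total. The t-based version gives 49 per arm, 98 in total, as stated. On dropout, "Assuming a scenario of around 20% dropout, we will need 126 participants": 98 / 0.80 = 122.5, so 123, close to 126. At 20% dropout about 126 × 0.80 = 101 complete, or roughly 50 per arm.

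**Part 1: the week-12 SE.** The correlations and SD patterns are my assumptions, as the documents give none. Let ρ be the correlation between adjacent visits, decaying with distance, and let visit k be the k-th follow-up (week 12 is k = 3). With baseline adjusted separately by visit:

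- residual variance at visit k: v_k = SD_k² × (1 − ρ^(2k)), and zero at week 0;
- model SE / true SE at week 12 = √(mean of v over the modelled rows / v_3);
- actual type I error = 2 × [1 − Φ(1.96 × ratio)].

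Example with constant SD, ρ = 0.6 and rows at weeks 4, 8 and 12: 1 − ρ^(2k) = 0.640, 0.870, 0.953, with mean 0.821. The ratio is √(0.821 / 0.953) = 0.928 and the type I error is 0.069. A week-0 row adds a zero, so the mean becomes 0.821 × 3/4 = 0.616, the ratio 0.804 and the error 0.115.

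| Outcome rows | SD pattern (mm) | Ratio, ρ = 0.6 / 0.75 | Type I error |
|---|---|---|---|
| Weeks 4-12 | constant 22 | 0.928 / 0.888 | 0.069 / 0.082 |
| Weeks 4-12 | 20, 22, 24 | 0.863 / 0.830 | 0.091 / 0.104 |
| Weeks 0-12 | constant 22 | 0.804 / 0.769 | 0.115 / 0.132 |
| Weeks 0-12 | 20, 22, 24 after baseline | 0.747 / 0.719 | 0.143 / 0.159 |
| Weeks 4-24 | constant 22 | 0.975 / 0.982 | 0.056 / 0.054 |
| Weeks 4-24 | 20, 22, then 24 | 0.945 / 0.956 | 0.064 / 0.061 |
| Weeks 4-24 | 19 rising by 1 to 24 | 1.011 / 1.025 | 0.048 / 0.044 |

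Adding a week-0 row to weeks 4-24 multiplies the last three rows by √(6/7) = 0.926. The ratios become 0.875 to 0.949, with type I error 0.063 to 0.087.

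On the scale of the margin, with SD 22.5 and 50 per arm, the true SE is 22.5 × √(2/50) = 4.50 mm and the 95% half-width is 1.96 × 4.50 = 8.8 mm. At a ratio of 0.83 the reported half-width is 7.3 mm. Yoga could then look up to 10 − 7.3 = 2.7 mm worse and still meet the 10 mm margin on a two-sided 95% interval, against 10 − 8.8 = 1.2 mm with the correct interval.

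**Part 2: the two-step rule.** Assume SD 22.5, correlation 0.6 between any two visits, 50 per arm, and true effects of 5, 10 and 15 mm at weeks 4, 8 and 12. Assume also that a significant interaction leads to the week-12 effect and a non-significant one to the average.

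- Interaction: sum of squared deviations from the mean effect = 25 + 0 + 25 = 50; within-participant variance = 506.25 × 0.4 = 202.5; noncentrality = (50/2) × 50 / 202.5 = 6.17 on 2 df; power about 60%.
- Fixed week-12 contrast: 15 / 4.50 = 3.33; power about 91%.
- Average: variance 506.25 × (1 + 2 × 0.6) / 3 = 371.25; SE √(371.25 × 2/50) = 3.85; 10 / 3.85 = 2.60; power about 74%.
- Two-step rule by simulation: it reports the 15 mm effect in about 60% of trials and the 10 mm average in about 40%. The mean reported effect is 13.7 mm, power about 87%, and type I error under the null about 5.4%.

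**The case against.** A reader might infer that the model understates the week-12 SE. The documents do not support that. It needs a week-12 variance above the average of the modelled visits, and no visit SDs are given. VAS over 24 weeks is a secondary outcome analysed with the same kind of model, so a fit through week 24 is at least as plausible as one that stops at week 12. There the error is small and can reverse. Unequal correlation alone does little harm to the week-12 test: with constant SD at the modelled visits and correlation 0.8 per visit, its type I error stayed at 0.049 to 0.052.

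The week-0 row is also only a possibility. Estimates at each time point and within-group differences point towards one, but the text also ties the treatment effect to each follow-up, and within-group change can be computed without such a row.

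A reader might also infer that the reported primary effect was picked by the interaction test. That is not so for the analysis used, which keeps the interaction and estimates each follow-up. The two-step defect lies in the original protocol text.

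Finally, the summary of changes says of the further covariates that "the results were similar to those of the unadjusted model, so we removed it from the model". One might read bias into this. The change is disclosed, the protocol promised only to assess those covariates, and nothing in the documents allows a bias to be quantified.

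These objections stand. They do not remove two facts: the covariance structure is restrictive and its outcome rows are unstated, and a step that changes the primary contrast disappeared without being logged. The residual plot that was inspected is not organised by visit, so it need not reveal a variance that changes over time.

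**Conclusion.** The point holds in two limited parts.

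First, the week-12 SE may be wrong, with direction and size unknown from the documents. Under the assumed correlations it is about 7-17% too small with weeks 4-12 as rows (type I error about 7-10%), about 20-28% too small with week 0 added to those rows (about 11-16%), and between about 5% too small and 3% too large with weeks 4-24 (about 4-6%). A claim that the interval is too narrow goes beyond the evidence.

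Second, the original protocol does not fix the primary contrast. Under the assumed effect path the cost is modest in power (about 87% against 91%) and small in type I error (about 5.4%), but the quantity reported would be 15 mm or 10 mm depending on a test. The analysis used avoids this. What remains is an ambiguous protocol and an unrecorded change.

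**What to change.** Name the group difference at week 12, from the model that always keeps treatment-by-visit, as the single primary contrast. Delete the main-effects step and enter its removal in the SAP summary of changes.

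State which visits are outcome rows and use post-baseline visits only. Put baseline VAS and baseline-by-visit in as covariates. Replace the default structure with an unstructured residual covariance by visit within participant, fitted by REML with small-sample degrees of freedom such as Kenward-Roger. The treatment-by-time interaction, baseline adjustment and REML are already in the described analysis, so the change is mainly to the covariance, the rows and the named contrast.

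Because the trial has been analysed, report this as a disclosed re-analysis for both the superiority and the non-inferiority conclusions, beside the results already obtained.

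The cost is a few lines of text and code, a few more variance parameters, which about 100 completers can support, and possibly a wider interval. If the variances really are constant over the modelled visits, little will change.

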#### **2. Binomial regression**

For the binomial regression, -glm function was used to estimate the risk ratio or risk difference by specifying the options family () and link (). Treatment group was included as the univariate predictor of OARSI-OMERACT responders.

- risk ratio by -glm with family (binomial) and link (log),
- risk difference by -glm with family (binomial) and link (identity).

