**Primary outcome:**

Change in knee pain assessed by VAS for over 12 weeks. Pain will be evaluated at each time point using a 100mm VAS and asked: “On this line, how would you rate your overall average knee pain in the last one week”? For knee pain assessed using VAS, terminal descriptors will be 0mm = no pain, 100mm = worst pain possible.

**Secondary outcomes:** (overall change from baseline to week 12 and overall change from baseline to week 24 are separate outcomes)

1. Change in VAS knee pain over 12 weeks in patients with painDETECT>12
2. Change in VAS knee pain over 24 weeks.
3. Change in WOMAC knee pain, WOMAC stiffness, and WOMAC knee function over 12 weeks and over 24 weeks.
4. Change in physical function as assessed by 30s Chair Stand Test, 40m Fast Walk Test and Stair Climb Test over 12 and over 24 weeks
5. OMERACT\_OARSI responders (meeting responder criteria) at week 12, and 24 weeks
6. Change in biomarker (urinary CTX-II, serum COMP, and serum hyaluronan) and systemic inflammatory markers (hs-CRP, IL-6, TNF- $\alpha$ ) over 12, and over 24 weeks
7. Change in Patient Health Questionnaire (PHQ-9) scales over 12, and over 24 weeks
8. Change in patient global satisfaction score over 12, and over 24 weeks
9. Change in painDETECT scores over 12, and over 24 weeks
10. Change in leg muscle strength (quadriceps) over 12, and over 24 weeks
11. Change in gait speed from baseline to week 12 and baseline to 24 weeks

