10. The OARSI-OMERACT responder criteria: This will be employed to generate a responder categorical variable (0 = non-responder, 1 = responder) based on improvement in WOMAC pain, function, and patient global assessment.
11. Change in QoL (assessed by AQoL-8D and EQ-5D-5L) from baseline to week 12 and baseline to 24 weeks.
12. Change in concomitant pain medications.

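### The OMERACT-OARSI responder comparison is unadjusted and uses no interim-visit data, although its component scales get both; it loses precision and is exposed to bias if dropout relates to response differently in the two arms

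*Combined protocol and SAP*

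**What the plan says.** The SAP part headed as the analysis used in the final manuscript describes two kinds of model.

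- **Responder outcome (section 2, Binomial regression).** "glm function was used to estimate the risk ratio or risk difference by specifying the options family () and link", with a log link for the ratio and an identity link for the difference. On predictors: "Treatment group was included as the univariate predictor of OARSI-OMERACT responders". No covariate, repeated-measures term or missing-data rule is given.
- **Continuous outcomes (section 1, Linear Mixed Effects Model).** "the model was also adjusted for baseline values for each continuous outcome, age, sex, and BMI". All visits are used under missing at random. The list of outcomes includes the WOMAC subscales and patient global assessment, but not responder status. The same section states: "no imputation procedures for missing data were performed, as these were not pre-specified in the original study protocol".

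The protocol's list of secondary outcomes sets the time points: "responders (meeting responder criteria) at week 12, and 24 weeks". Item 10 of the SAP's secondary outcomes says that the variable is "based on improvement in WOMAC pain, function, and patient global assessment". The visit schedule in the protocol has knee WOMAC and patient global at baseline and at weeks 4, 8, 12, 16, 20 and 24.

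**The concern.** The same three scales are handled in two ways. Someone with week 4 and week 8 scores but none at week 12 informs the mixed-model results for WOMAC pain, WOMAC function and patient global. That person appears to contribute nothing to the week 12 responder result built from those scales.

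Two things are at stake. The first is precision: baseline and interim scores predict later scores, and the responder model uses neither as a predictor. The second is bias: if people who are not improving leave one arm more readily than the other, the responder rate among those who stay is inflated more in that arm.

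**Working it through.** **1. The plan's own figures.** The documents give no rate, power or precision for the responder outcome. The nearest figures are in the sample size section: difference 15 mm, SD 22.5, two-sided 0.05, 90% power, 98 evaluable, 126 with about 20% dropout.
- Normal approximation: 2 × (1.960 + 1.282)² × (22.5/15)² = 47.3, so 48 per arm and 96 in total. The t-based version gives 48.3, so 49 per arm and 98 in total, as stated.
- 98/0.80 = 122.5, so 123; the stated 126 is slightly above this.
- At 20% dropout, 126 × 0.80 = 100.8, so about 101 remain for the responder comparison.

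**2. Precision of the univariate risk difference.** Assume 50% response in both arms. The 95% half-width is 1.96 × √(2p(1−p)/(N/2)).
- N = 126: 17.5 points.
- N = 100.8: 19.5 points.
- The pair is 17.1 and 19.1 at 40% or 60% response, and 16.0 and 17.9 at 70%.

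**3. Bias by arithmetic.** Let p be the true response rate in an arm, d its dropout proportion and q the response rate among dropouts. The rate among those who stay is (p − dq)/(1 − d). Take p = 50% in both arms and 20% dropout overall; all by-arm inputs are assumptions.
- Moderate case, dropout 15% v 25%, q = 30%: (50 − 4.5)/0.85 = 53.5 and (50 − 7.5)/0.75 = 56.7, a false difference of 3.1 points.
- Extreme case, dropout 10% v 30%, q = 20%: (50 − 2)/0.90 = 53.3 and (50 − 6)/0.70 = 62.9, a false difference of 9.5 points.
- If q = p, the formula returns p whatever d is. Unequal dropout alone does no harm.

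**4. Simulation.** 126 participants, 1:1, no true difference, about 20% missing at week 12, 1,500 runs per setting. Assumptions: correlation between visits of 0.4 or 0.6; response means that one improvement score passes a threshold met by 50%, a simplification of the three-component rule. Imputation used arm, baseline and weeks 4 and 8, with 20 imputations. Dropout was random, or depended on week 8 improvement in the same way in both arms, or did so in one arm only. Bias is the mean complete-case difference minus the mean full-data difference in the same runs, in points. SDs are of the risk difference, in points.

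| Correlation, dropout | Bias, complete case | SD, complete case | SD, complete case + baseline | SD, imputed | SD, imputed + baseline |
|---|---|---|---|---|---|
| 0.4, random | −0.1 | 9.8 | 9.2 | 8.9 | 8.3 |
| 0.4, same in both arms | −0.2 | 10.3 | 9.1 | 9.4 | 8.3 |
| 0.4, one arm only | 4.4 | 10.0 | 9.3 | 9.1 | 8.4 |
| 0.6, random | 0.0 | 9.9 | 9.3 | 8.9 | 8.4 |
| 0.6, same in both arms | 0.1 | 9.8 | 9.3 | 9.1 | 8.6 |
| 0.6, one arm only | 3.6 | 10.1 | 9.5 | 9.2 | 8.6 |

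- From complete case to imputed plus baseline, the smallest SD reduction is 1 − 0.0858/0.0977 = 12% and the largest is 1 − 0.0834/0.1028 = 19%.
- In the one-arm settings, imputation plus adjustment brought the bias to within 0.2 points of zero. Dropout there depended on an observed score, which is the case imputation is built for.

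**The case against.** The other side has good points, and several stand.

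- **Exclusion is inferred.** A reader might take the plan to state that participants without week 12 or 24 data are dropped. It does not. The binomial section is silent, and the no-imputation sentence sits under the mixed model. A glm with one binary outcome per person and no imputation leads there in practice, but this is an inference.
- **Baseline is not ignored.** A responder is defined by improvement, so baseline scores enter every classification. What is missing is their use as covariates.
- **The assumption needed is weaker than it may seem.** One might say that the analysis requires data missing completely at random. Missingness unrelated to response within each arm is enough, and with complete data the unadjusted contrast is valid under randomisation.
- **Interim data on dropouts may be limited.** The documents do not say when participants left. Anyone leaving before week 4 contributes only baseline.
- **The components are already analysed well.** All three are in the mixed model, so the responder result is a supplementary dichotomy of them.

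The plan's reason for not imputing, that it was not pre-specified, carries less weight here. The protocol's statistical section and the SAP's data analysis section describe a model for continuous outcomes and none for the binary responder outcome. The univariate glm first appears in the account of the final analysis, so it has no pre-specification advantage. Still, replacing a reported result after the fact would be wrong; a better analysis belongs beside it.

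**Conclusion.** The point holds in a limited form. The responder analysis lacks the baseline adjustment and interim-visit information that its own components receive. The cost in precision is about 12–19% of the SD of the risk difference, on assumed correlations, a 50% response rate and 20% dropout.

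Bias is a risk and has not been shown. It is about 3–4 points in the moderate cases examined, small beside a 95% half-width of about 19.5 points, and near zero when there is no true difference and dropout works the same way in both arms. A reader might infer a false difference near 10 points. The arithmetic allows 9.5, but only with threefold differential dropout and dropouts responding at 20%, and the documents give no dropout by arm. Nor does that example show that imputation would remove the bias, since it does not say whether earlier visits explain the poor response of dropouts.

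This is a secondary outcome. Nothing here bears on the primary VAS conclusion.

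**What to change.** Add one analysis of responder status and keep the univariate result where it is.

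1. Impute WOMAC pain, WOMAC function and patient global by arm, using baseline and all visits, and derive responder status in each imputed data set.
2. Fit a model for response with treatment, baseline WOMAC pain, function and global, age, sex and BMI, matching the covariates of the continuous models.
3. Report the standardised risk ratio and risk difference at weeks 12 and 24, labelled post hoc, beside the univariate estimates.
4. Report responder denominators and missing counts by arm at both visits, and state how missing responder data were handled in the univariate model.

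The cost is a little extra analysis work on data already collected, plus reliance on the missing-at-random assumption already made for the continuous outcomes. If the added analysis is not done, item 4 alone would let readers judge the exposure to dropout.
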